#### Missing data

To account for missing data, we will use multiple imputation by chained equations methods of Raghunathan et al. for primary analyses [136]. In sensitivity analyses, we will perform complete case analyses with the anticipation that doing so will confirm the conclusion.

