Similarly, how best to communicate genetic research results to research participants remains unclear. Unlike patients with clinical genetic testing, research participants may not be prepared for actionable results, particularly if the results are unrelated to the reason they enrolled in research, or if they enrolled as healthy unselected participants many years prior (e.g. large biobanks). While having GCs disclose these results may be ideal to ensure understanding, minimize psychosocial distress, and optimize medical follow-up and cascade testing [43], GC workforce shortages and costs are barriers [43, 44]. Many programs have used GCs to share genetic research results [8, 35, 37, 45–47], while others have provide results to local health care providers [48, 49] who may lack the necessary expertise or resources, resulting in suboptimal patient outcomes [50]. Interactive patient-centered digital interventions and/or videos developed by genetic providers may provide a cost-effective alternative [51–54]. Further, these interventions could be paired with genetic counseling for participants with remaining questions, while still reducing overall provider time. Potential disadvantages include poor understanding, increased test-related short-term and/or long-term affective responses or suboptimal post-test behaviors (e.g. medical management and cascade testing). Limited data exist on patient outcomes, clinical outcomes, and costs associated with various approaches. Empirical data are needed to inform best approaches for pre-disclosure education and returning results to realize benefits for participants.

Although research participants have reported high interest in receiving research results [15, 48, 55–62], uptake has been lower when results have been offered (48–86%), particularly in biobank studies where return of results was not emphasized during enrollment and uptake has generally been around 50% [36, 38, 63–69]. There are limited patient-reported outcomes in research settings [63–65, 70], although some genomic implementation studies report no psychological harms with return of genetic findings [71, 72]. In the RESPECT2 study, research participants could choose pre-disclosure education with a GC or a patient-centered digital intervention. All participants received results with a GC. Favorable cognitive (e.g. knowledge) and affective (e.g. distress and uncertainty) responses were found, although the number of actionable results was small [73, 74]. 

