### Ethics approval

The original PMBB consent stipulated that actionable results would be returned but did not describe the various types of results or when and how these would be returned. It also did not specify how one might decline (e.g. opt out of) results. Thus, the Return of Results (ROR) protocol is an extension of the original PMBB protocol and consent process. It is not “a new study” but rather is a process for implementing the obligation that was already established in the PMBB consent, when it was stated that results that could impact one’s health would be returned. Thus, the ROR process provides PMBB participants with current and comprehensive information on what results are being returned and how and the opportunity to decline these results if they desire. These activities (with the exception of the surveys) are all a direct extension of the obligation set in the original consent regarding results. We do require an informed consent for the surveys, but if a participant declines the surveys, we are still bound by the original PMBB consent to provide actionable results as previously stated. The participants will receive a $50 gift card for each survey completed.

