### Data analysis plan

#### Primary non-inferiority analyses

We hypothesize that disclosure of actionable results by digital-ROR, with access to a GC, can provide non-inferior short-term and longitudinal cognitive, affective, and behavioral outcomes, and lower costs. Primary effectiveness outcomes include: post-disclosure knowledge and cancer or cardio disease-specific distress. We will test whether the receipt of results differ between arms as a secondary analysis. Receipt of results is considered a health behavior. For the 2 primary analyses, we will apply non-inferiority tests to examine if access to digital-ROR is non-inferior to GC disclosure. We will conclude non-inferiority if the upper bound of the randomization effect 97.5% one-sided confidence interval [CI] for cross-sectional T1 responses do not cross a -0.45 standardized difference threshold (i.e., margin) for knowledge and a 0.2 standardized threshold (i.e., margin) for disease-specific distress in the direction that would suggest that digital-ROR is worse. A standardized difference is the difference after variables are scaled to have standard deviation (SD) one with respect to baseline SD. We based the margins on what might be considered clinically relevant effects given our pilot data. We will use intention-to-treat approaches, comparing randomized arms, with confirmation by per-protocol analyses (i.e. restricting sample to those who properly used the method of disclosure as assigned). We will only declare non-inferiority if both intention-to-treat and per-protocol analyses are consistent, as recommended [133, 134]. For the secondary outcome receipt of results, we will examine non-inferiority of proportions. We will declare non-inferiority if the upper bound of the randomization effect 95% one-sided confidence interval for receipt of results is < 10% in the direction that favors usual care. Since all participants will have the option to speak with a GC, we will conduct secondary as-treated analyses (i.e. based on whether genetic counseling was actually received in both arms).

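### The complete-case check named for missing T1 data shares the main weakness of the imputation it is meant to test, so their agreement would be weak evidence for non-inferiority

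*Protocol article*

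**What the plan says.** **Missing data.** For the primary analyses "we will use multiple imputation by chained equations methods". The sensitivity analysis is stated as: "In sensitivity analyses, we will perform complete case analyses with the anticipation that doing so will confirm the conclusion". The article names no analysis that lets missing participants differ systematically from observed ones.

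**Analysis sets.** Primary non-inferiority analyses states: "We will use intention-to-treat approaches, comparing randomized arms, with confirmation by per-protocol analyses". Per-protocol means "restricting sample to those who properly used the method of disclosure as assigned". Non-inferiority is declared only if the two are consistent. A secondary as-treated analysis is "based on whether genetic counseling was actually received in both arms".

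**Where missing T1 can arise.**
- T1 is taken 2-7 days after disclosure (Uptake of results and patient reported outcomes).
- Randomisation comes before the Step 2 letter and so before disclosure (Randomization). People who never collect results are foreseen and sent a closing letter (Non-response procedures).
- Surveys need separate consent: "We do require an informed consent for the surveys, but if a participant declines the surveys, we are still bound" to return results (Ethics approval).
- In earlier biobank studies "uptake has generally been around 50" per cent (Background). Sample size justification for aim 1 takes a receipt rate above 55% as promising.

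**The concern.** A sensitivity analysis earns its place by resting on a different assumption from the primary one. Chained-equation imputation, as normally run, assumes that a missing T1 score resembles the observed scores of people in the same arm with similar baseline data. Complete case compares the observed people directly. Neither allows for missing digital-arm participants who fare worse than their baseline data predict, so in that situation both give a similar, and similarly wrong, answer.

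The remaining analyses do not fill the gap. Per-protocol excludes those who never used the assigned method and says nothing new about people who received results but did not answer. As-treated regroups people by counselling received. The uptake outcome shows how many did not receive results, not how they fare.

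Background lists poor understanding and stronger affective responses as possible drawbacks of digital delivery. These correspond to the two primary outcomes. If either also leads people to drop out of the digital process or skip the survey, the loss is informative, and in a non-inferiority trial it would favour the new method.

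**Working it through.** **Inputs from Table 4 and Sample size justification for aim 1.** 255 per arm; one-sided 2.5% per outcome. Knowledge: margin 0.45 x 2.86 = 1.287 points, T1 SDs 2.59 and 2.12, pilot effect -0.7. Distress: margin 0.20 x 9.31 = 1.862 points, T1 SDs 5.72 and 6.42, pilot effect -0.22.

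**Assumptions, not in the article.** The missing share f of T1 (20% and 45% shown; 45% is the complement of 55% receipt), equal in both arms, and the amount delta by which missing digital-arm participants are worse than imputed. It is unclear whether 255 per arm means randomised or with T1, so both are shown. 255 with T1 at 45% missing implies 255/0.55 = about 464 randomised per arm, a figure the article does not give.

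**1. The plan's own power.** SE = sqrt((SD1² + SD2²)/n). At n = 255, knowledge SE = sqrt(11.2025/255) = 0.210 and distress SE = sqrt(73.9348/255) = 0.538. Power = Phi((margin - worsening)/SE - 1.96).

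| Outcome, assumed effect | Recomputed | Table 4 |
|---|---|---|
| Knowledge, -0.7 | 80.0% | > 80% |
| Knowledge, 0 | > 99.9% | > 99% |
| Distress, -0.22 | 97.2% | > 95% |
| Distress, 0 | 93.3% | > 90% |

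Table 4 reproduces to rounding from the T1 SDs.

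**2. False non-inferiority when the missing are half a margin worse.** Set the true all-randomised difference at the margin. The estimate is too favourable by f x delta, so the error rate is Phi(f x delta/SE - 1.96). Delta is 1.287/2 = 0.6435 for knowledge and 1.862/2 = 0.931 for distress. Example, knowledge, f = 0.45, n = 255: 0.45 x 0.6435 = 0.290; 0.290/0.210 = 1.38; Phi(1.38 - 1.96) = 0.281.

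| Outcome | 20% missing (n = 204 to 255 observed per arm) | 45% missing (n = 140 to 255) |
|---|---|---|
| Knowledge | 7.9% to 8.9% | 17.5% to 28.1% |
| Distress | 4.9% to 5.3% | 8.3% to 11.9% |

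The nominal rate is 2.5%. These rates are for the intention-to-treat test alone.

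**3. Shift that would overturn non-inferiority at the pilot effects.** Tipping shift = (margin - confidence bound)/f, in points. The first figure is for 255 randomised per arm, the second for 255 with T1.

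| Missing | Knowledge (-0.7) | Distress (-0.22) |
|---|---|---|
| 20% | 0.64 / 0.88 | 4.5 / 5.1 |
| 30% | 0.32 / 0.59 | 2.7 / 3.4 |
| 45% | 0.07 / 0.39 | 1.5 / 2.3 |

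With no true knowledge difference at 45% missing, the knowledge shift is 1.6 / 2.0 points. Robustness therefore depends heavily on the missing share and on the observed effect.

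**4. Do imputation and complete case disagree when both are wrong?** Simulation: 1,000 runs, 255 randomised per arm, imputation on arm and baseline, assumed baseline-T1 correlation 0.5. The true difference is at the margin and all the harm sits in missing digital-arm participants. Both methods estimated a difference near 0. Distress non-inferiority was declared at 20%, 30% and 45% missing in 88%, 85% and 74% of runs by imputation, and in 88%, 83% and 72% by complete case. For knowledge both exceeded 99%. This is a deliberate stress case. It shows a shared blind spot and does not forecast an error rate.

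**The case against.** Several objections have force.

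- **The article is a summary.** A fuller analysis plan may contain a tipping-point analysis. A reader might infer that complete case is the only check the trial has; that can be said only of this article. What stands is that the article does name a check and a purpose for it, and the check does not suit the purpose.
- **Differential uptake.** A reader might infer that the plan expects receipt to differ by arm. It does not. It tests for a difference under a non-inferiority criterion, and the Discussion anticipates equal or better outcomes with digital delivery.
- **Direction of bias.** A reader might infer that imputation favours digital-ROR. The documents do not show this. People who never open their result cannot be distressed by its content, digital-arm participants can ask for a counsellor before or after results, and follow-up of non-responders is described for both arms. The bias could be nil or run the other way.
- **Complete case is not empty.** If missingness depends on baseline scores, unadjusted complete case and imputation can diverge, so it is a limited but real check.
- **The share imputed is inferred.** The primary outcomes are described as measured after receipt of results, and the interim analysis counted T1 completers. If people who never receive results are outside the T1 analysis, the 45% scenario falls away and only survey non-response remains, for which no rate is given. Against this, "We will use intention-to-treat approaches, comparing randomized arms" reads most naturally as everyone randomised.
- **Estimand.** Post-disclosure outcomes are not observed by design for people who never receive results, and shifting their imputed values does not settle what is being estimated. This is correct, and it is why the two kinds of missingness need separating.
- **Joint rule.** Requiring per-protocol agreement can only lower the rates in step 2, so they are upper bounds for the stated scenarios.

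**Conclusion.** The point holds in limited form and should be addressed. In this article, the check named for missing T1 data cannot detect worse outcomes among missing digital-arm participants with similar baseline data, and per-protocol excludes those who never used the assigned method. Agreement among these analyses is therefore weak evidence of robustness.

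The possible size is material for knowledge and smaller for distress at the half-margin shift. It rests on an assumed missing share, an assumed half-margin shift confined to the digital arm, and the intention-to-treat test alone. It does not show that the trial's conclusion will be biased, or in which direction.

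**What to change.** Keep chained-equation imputation, run separately by arm, as primary, and keep complete case as descriptive. Before the final analysis, pre-specify:

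1. A delta-adjusted tipping-point analysis that worsens imputed digital-arm T1 values from 0 to one margin (1.29 knowledge points, 1.86 distress points). Report beside the primary interval the shift at which non-inferiority is lost, or state that it survives the whole range.
2. T1 missingness by arm, split into no disclosure and disclosure without a survey, with the shifts applied separately to the two groups.
3. A statement of whether 255 per arm means randomised or with T1, and whether people who never receive results belong to the primary T1 comparison.

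In Missing data, drop the wording that anticipates confirmation. The cost is a short addition to the analysis plan and some code, with no new data or change in conduct. The conclusion may need qualifying if a small shift overturns it.

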#### Interim analyses

We conducted an interim analysis after 100 people per arm had been enrolled and completed the T1 post-disclosure survey (200 total who have completed the T1 survey). We constructed the interim analysis to protect the Type I error rate. We did not pause the study based on the interim analysis.

#### Aim 2 analyses

Estimation of the proportion opting out will constitute our primary Aim 2 analysis and estimation of the proportion with uptake of supplemental digital education will constitute our secondary Aim 2 analysis. We will also estimate 95% confidence intervals with the proportions. For our primary Aim 2 analysis, we will test whether the proportion opting out is 5% using a one sample binomial exact test. We will primarily assess the proportions opting out with respect to those who are evaluable (i.e., alive and who do not have returned mail). We will subsequently assess proportions among those evaluable and who have an actionable result (secondary analysis). We will also compare opt-out between cases and controls.

For our secondary Aim 2 analysis, uptake of digital education will be classified as (1) accessing digital education, and (2) completing digital education. Secondary outcomes of education uptake will include (3) the platform used (web or chatbot), (4) # of visits to digital education, (5) total time, and (6) accessing videos. We will describe secondary outcomes using means and standard deviations (e.g., time and # of visits) or proportions (e.g., accessing individual videos) as appropriate. To evaluate the impact of completing education on opting out, we will compare opt-out rates between those who do and those who do not access and complete digital education using Fisher’s Exact Tests (Aim 2c). In secondary analyses, we will use generalized linear models with appropriate link and family functions for Aim 2 endpoints (e.g., Poisson regressions for # of visits, linear regressions for baseline patient reported outcomes). We will enter confounders into the models. We will examine models separately for those who did and those who did not receive letter 1 or letter 2.

#### Sample size justification for aim 2

We anticipate an approximate 5% opt-out rate based on our pilot data. With at least 1250 participants (and up to 2500 participants), we will be able to test whether the rate is < 5% (null hypothesis) versus > 7.5% (alternative hypothesis) with 95% power and a 2.2% Type I error rate (one-sided), and the use of a one-sample binomial test.

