#### Randomization

After at least 4 weeks, participants with an actionable finding (cases) who have not chosen to opt-out of receiving their results are randomized to receive their results by remote telehealth disclosure with a GC (Arm 1) or by a private ROR digital intervention (Digital-ROR) with the option to schedule a call with a GC at any time in the process (Arm 2). A permuted block design is used for randomization, stratifying by cancer or cardiovascular genes and sex.

Randomized participants are sent the Step 2 Letter by MyPennMedicine portal (MPM), encrypted email or mail informing them that an actionable genetic finding that could potentially impact their health has been identified (Supplemental Fig. 2). The letter includes how they will receive their actionable results (according to their randomization), the next steps for receiving results and that they can still elect to NOT receive results. Procedural controls do not receive the Step 2 Letter, but any who opt-out of results after the Step 1 Letter has their decision recorded in case they are found to have an actionable result with additional sequencing or analysis.

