#### Uptake of results and patient reported outcomes (aims 1 and 2)

Theoretically informed patient-reported cognitive, affective and behavioral outcomes of genetic services are collected at baseline (T0), 2–7 days post-disclosure (T1) and at 6 months (T2).

Knowledge of genetic disease (primary non-inferiority outcome) is evaluated at all time points (T0-T2) using an adapted version of the KnowGene Scale, a 16-item scale administered to patients after genetic testing and/or genetic counseling to measure their understanding of the health implications of genetic test results [111]. It includes health implications to oneself as well as relatives. This measure covers penetrance, actionability, limitations of current technology, and monogenic inheritance patterns. Items 3, 5, 13 and 15 were excluded as they are not relevant to return of actionable results. Additionally, 4 items evaluating understanding of the difference between research and clinical testing and utilized in the RESPECT2 study were added to create a final scale of 16 items. This adapted scale has had good internal consistency in our pilot and related studies (Cronbach’s α = 0.63–0.83) [79, 112]. Perceived risk of cancer and cardiovascular disease (T0-T2) is evaluated with a numerical scale (risk 0-100%) and an 5-point verbal scale (much lower than average risk to much higher than average risk) as utilized in our related studies. The 8-item Attitudes Toward Genetic Testing scale is assessed at baseline to understand perceptions of genetic testing and to assess informed choice in combination with genetic knowledge and decisions to proceed with testing, as previously utilized in the multi-dimensional measure of informed choice and our related research (Cronbach’s α = 0.73) [113–115]. *Reactions to genetic information* are assessed with multiple instruments that evaluate psychological distress, adjustment and satisfaction. (a) Disease-specific distress (primary non-inferiority outcome) is measured at all timepoints (T0-T2) using the 8-item version of the Revised Impact of Events Scale (RIES) [94, 116–121], evaluating intrusive and avoidant thoughts regarding cancer and cardiovascular disease separately. The 8 item scale has strong internal consistency in related studies and our pilot study (Cronbach’s α = 0.70–0.92) [122, 123]. (b) *General anxiety and depression* are assessed by the respective 4-item short Patient Reported Outcomes Measurement Information System (PROMIS) scales (Cronbach’s α = 0.88 and 0.86) [79, 124]. (c) *Satisfaction with genetic services* (T1 only) will be assessed with a 14-item satisfaction with communication scale, and adapted for telehealth and digital disclosure, evaluating participants’ experience with high internal consistency in our related studies (Cronbach’s α = 0.73–0.85) [112, 114, 125] (d) *Multidimensional responses to genetic testing*, including positive responses and uncertainty, are assessed at T1 and T2 using the 20 items from the Multi-dimensional Impact of Cancer Risk Assessment Questionnaire (MICRA) with strong internal consistency in our pilot study by subscales (Cronbach’s α = 0.77–0.85) [79, 126]. (e) Decisional regret (T1, T2) is assessed using with the 5-item validated Decision Regret Scale used in genetic studies [127, 128]. This scale has had strong internal consistency in our pilot study (Cronbach’s α = 0.86) [79]. *Use of genetic information* includes uptake of receipt of actionable research results and other health and communication behaviors. (a) *Uptake of research results (secondary non-inferiority outcome)* will be assessed as completion of a remote telehealth disclosure session with a GC (either arm) or as viewing results in digital-ROR (digital arm). Other secondary uptake behaviors include uptake of supplemental digital education (Aim 2a), assessed as completion of pre-disclosure digital education or Chat 1, actively opting-out of receipt of research results after the Step 1 or Step 2 Letter (Aim 2b), completion of confirmation testing, and completion of clinical genetics follow-up, either by documentation in the EHR or self-report by those who are no longer in the local area. (b) Risk reducing behavioral intention (T1 only) and performance (T2) will be assessed with a close-ended and open –ended items given a lack of established measures and the wide range of potential medical management options depending on the individual gene. General health status and risk modifying behaviors (e.g. diet, exercise, tobacco and alcohol use) will be assessed at baseline and at T2 with items utilized in BRFSS and related studies [73, 125, 129]. Additionally, gene-specific medical management or risk reducing screening and interventions will be abstracted from medical records. (c) Communication of genetic test results includes communication intent (T1 only) and performance (T2) assessed using a 3-item measure of intent and communication to assess intent to share genetic test results with health care providers, family members and other third parties utilized in related research [85–87]. 

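### Cases can opt out after two letters and procedural controls after one, so the planned case-control comparison of opt-out has a difference built in

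*Protocol article*

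**What the plan says.** Four statements in the protocol article have to be read together.

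- **Definition of the outcome** (Uptake of results and patient reported outcomes): the Aim 2b behaviour is "actively opting-out of receipt of research results after the Step 1 or Step 2 Letter (Aim 2b".
- **Who gets which letter** (Randomization): "After at least 4 weeks, participants with an actionable finding (cases) who have not chosen to opt-out of receiving their results are randomized". These cases are sent the Step 2 Letter, which tells them of an actionable finding and sets out "the next steps for receiving results and that they can still elect to NOT receive results". For the other group, "Procedural controls do not receive the Step 2 Letter".
- **Case-control contrast** (Aim 2 analyses): "We will also compare opt-out between cases and controls". The sentence names no letter stage or time window.
- **Primary Aim 2 test** (Aim 2 analyses): "we will test whether the proportion opting out is 5% using a one sample binomial exact test". The main denominator is everyone evaluable, cases and controls together. A cases-only proportion is secondary. The sample size section for Aim 2 bases the 5% on pilot data.

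**The concern.** At Step 1 neither group has been told its status, and both get the same letter, so opt-out rates from that stage can be compared directly. The stated outcome goes further. It adds, for cases only, a second occasion that comes after notification. The non-response procedures then follow up cases who have neither received results nor declined. Controls have no counterpart to any of this.

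If cases and controls behave identically at Step 1, a single Step 2 refusal is enough to put the expected case rate above the control rate. The contrast could then be taken to mean that the two groups differ in their wish to receive results, when it reflects only the extra letter.

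The same definition feeds the primary Aim 2 proportion. That proportion averages a group with one opportunity and a group with two, in a ratio set by how many controls the team contacts. The article does not state the ratio.

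**Working it through.** **Inputs from the article.** Reference rate 5%, alternative 7.5%, n from 1250 to 2500, one-sided type I error 2.2%, power 95% (sample size justification for Aim 2). Up to 2500 cases and controls are to be contacted (Enrollment goals).

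**Assumptions, because the article does not give them.** Step 1 opt-out p = 5% in both groups. Step 2 opt-out q among cases who did not decline at Step 1, varied over 1%, 2% and 3%. Group sizes of 625 or 1250 each. Case share s of 20%, 50% or 80%. Fisher's exact test, two-sided 5%, for the case-control contrast; the article names that test for related Aim 2 comparisons but names none for this one.

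**1. The plan's own figure.** For X ~ Binomial(1250, 0.05), P(X ≥ 79) = 0.0217 and P(X ≥ 78) = 0.0288, so the rule is to reject at 79 or more opt-outs. At 7.5%, P(X ≥ 79) = 0.952. The stated 2.2% and 95% reproduce.

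**2. Case-control comparison.** The case rate is p + (1 − p)q = 0.05 + 0.95q, and the control rate stays at 0.05. The rejection probability was obtained by summing over both binomial distributions.

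| q | Case rate | Control rate | 625 vs 625 | 1250 vs 1250 |
|---|---|---|---|---|
| 0 (Step 1 only) | 5.00% | 5.00% | 4% | 4% |
| 1% | 5.95% | 5.00% | 9% | 16% |
| 2% | 6.90% | 5.00% | 26% | 49% |
| 3% | 7.85% | 5.00% | 50% | 81% |

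Step 1 behaviour is the same in both groups in every row.

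**3. Pooled proportion, n = 1250, reject at 79 or more.** The pooled rate is s(0.05 + 0.95q) + (1 − s)(0.05) = 0.05 + 0.95qs. At q = 2% this is 0.05 + 0.019s.

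| Case share s | Pooled rate, q = 2% | Rejection, q = 2% | Rejection, q = 1% |
|---|---|---|---|
| 20% | 5.38% | 8% | 4% |
| 50% | 5.95% | 31% | 11% |
| 80% | 6.52% | 63% | 21% |

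Within each value of q, participants behave the same at every case share; only the recruitment mix changes. With q = 0 the rejection rate is 2.2% at any mix.

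**4. Do the other planned analyses repair the contrast?** The cases-only proportion is free of mixing but involves no controls. The article also plans to examine models separately by receipt of letter 1 or letter 2. No control receives letter 2, and the cases who do not receive it are largely those who declined at Step 1, so that stratum is selected on the outcome itself.

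**The case against.** The strongest reply is that the case-control comparison is one secondary sentence with no hypothesis, test or window. The outcomes section may only list when opt-outs are captured, and the full protocol or SAP may choose the stage. This stands in part: the contrast is minor, and a descriptive comparison that includes the reaction to notification would be legitimate if labelled so. But the article does give a definition, and it names both letters. An SAP that used Step 1 alone would depart from it.

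A second reply is that equal Step 1 rates are assumed. Cases may differ in personal or family history, and how controls are selected is not described. That is correct, and it is a further reason to isolate Step 1, where a real difference could be seen without the second letter on top of it.

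A third reply concerns the pooled test. A reader might infer that the test against 5% is biased or has an inflated type I error. At q = 3% and half cases, for example, it rejects in 58% of trials. The article does not support that reading. The pooled rate is then 0.05 + 0.95 × 0.03 × 0.5 = 6.4%, the null hypothesis is false, and rejection is power. It would be an error only if the pilot 5% meant Step 1 opt-out or came from a different mix, and the article says neither. This reply stands in full. What remains is that the result depends on the case share.

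**Conclusion.** As written, the case-control comparison does not compare like with like. The expected case rate exceeds the control rate by 0.95q when Step 1 opt-out is 5% in both groups. The chance of a significant difference from the second letter alone runs from 9% at q = 1% with 625 per group to 81% at q = 3% with 1250 per group, against about 4% for Step 1 only. These sizes rest on assumed Step 2 rates and group sizes. The direction needs only some Step 2 opt-out and equal Step 1 behaviour.

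The pooled 5% test is sound for the proportion it defines, and its error rate and power reproduce. Its weakness is interpretation: the proportion depends on an unstated mix, and the stage and mix behind the 5% are not given. Aim 1 is not affected.

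**What to change.** 1. For the case-control comparison, count only Step 1 opt-outs, in one window of the same length for everyone that starts with the Step 1 Letter and closes before any Step 2 Letter. The four-week minimum before randomisation is one possible window, not the only one.
2. Report Step 2 opt-out separately, with the cases who were sent the Step 2 Letter as denominator.
3. For the 5% test, state which letter stage and which mix of cases and controls the pilot 5% refers to, and use the matching definition. If the result should not depend on the case share, that definition is Step 1 opt-out.

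The cost is wording, plus the dates of letters and opt-outs, which the two-step process should already record. The drawback is that opt-outs after the common window drop out of the case-control comparison and have to be reported separately.
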